**Fig. 1 Fig1:**
[figure not shown]
Trial flowchart

Patients in the cognitive-motor training group will carry out both the cognitive and the motor training programme, while patients in the cognitive training group and the motor training group will respectively carry out only the cognitive training programme and the motor training programme (see Fig. 1). Before the start of the training, a start-up teleconsultation with an MS nurse will be scheduled, where patients will receive clear instructions on how to carry out the training programme(s).

For the cognitive treatment intervention, we will use the widely used cognitive training programme RehaCom® (Hasomed GmbH, Magdeburg, Germany). This is a computer-aided programme with more than 30 modules focusing on different domains of cognition. RehaCom has shown improvements in verbal learning, visuospatial memory, information processing speed, attention, executive functions, depression, fatigue and quality of life in PwMS [35–38]. Patients will train on their home computer without direct therapist supervision, using three RehaCom modules (Working Memory, Topological Memory and Shopping) that are focused on improving working memory. Both patients in the combined intervention and the cognitive intervention group will be doing a 45-min computer session respectively 1 and 2 days per week for a total of 12 weeks. During one 45-min training session, patients will complete 15 min of exercises of each of the three modules. The level of difficulty of the exercises is automatically adapted to the patient’s performance.

For the motor training, we will use a patient-tailored training programme based on the patient’s baseline activity level. At inclusion, all patients will complete the Godin Leisure-Time Exercise Questionnaire (GLTEQ) to assess their level of activity and be divided into three groups (see Fig. 2) [39]. Based on their baseline physical activity level, patients can choose from a number of aerobic activities of either mild, moderate or strenuous intensity, with a total training time of 90 min per week for the motor training group and 45 min for the combined cognitive-motor training group, divided over at least two training sessions per week of at least 15 min per session (see Fig. 2). The training will be carried out individually at home, without therapist supervision. Patients will use a heart rate sensor to maintain the correct training intensity, with 20–39%, 40–59% and 60–84% of their heart rate reserve (target heart rate = *heart rate reserve*X% intensity + resting heart rate; heart rate reserve* = *maximum heart rate − resting heart rate*; *maximum heart rate = 220 − age* [40]) respectively corresponding to mild, moderate and strenuous training [41–43]. Heart rate will be monitored using a sport watch (Polar Unite, Polar Electro, Kempele, Finland), provided by the research team and equipped with an accelerometer and a heart rate sensor. Furthermore, patients will be asked to rate the training intensity with the Rating of Perceived Exertion scale (RPE [44]). A score of 10–11, 12–13 and 14–16 corresponds to mild, moderate and strenuous training respectively [41, 42]. Both baseline activities and training activities in the context of the study will be logged using the sports watch. In order to ensure that activity levels remain the same in the group receiving only cognitive training, the activity levels of these patients will be monitored as well. Adaptations to training intensity in response to issues reported by patients will be decided on a case-by-case basis.

**Fig. 2 Fig2:**
[figure not shown]
Motor training algorithm

Participants will have a 20-min teleconsultation once every 2 weeks with a trained MS nurse. The teleconsultations will take place using Microsoft Teams® (Microsoft Corporation, Redmond, WA, USA) and the patient can use any device equipped with a webcam and microphone. The consultations consist of a structured interview dealing with motivation of the patient to continue the training, perceived impact of cognitive and physical difficulties on the patient’s life in the past weeks, effort applied to the training in the previous weeks, technical difficulties experienced, targets for next weeks’ training, and additional questions by the patient. Adherence to the training programmes will be assessed through a RehaCom therapist account for the cognitive training and through a Polar Flow for Coach account for the motor training.

### Primary outcome parameter

The primary outcome measure is the digit span backwards test [33], which assesses working memory. The examiner produces a list of digits at a rate of one digit per second and patients have to repeat the list in reverse order. Two trials are presented for each span length. If patients fail two trials of the same span length, the test is ended. The test starts with a list of two items and gradually increases to a maximum of eight items. Based on clinical experience, we will consider an improvement of one point on this test a clinically significant difference. This test will be carried out at the start of the trial, after 12 weeks of training, at 24 weeks and 64 weeks.

### Secondary outcome parameters

The following secondary clinical outcome measures will be assessed: Expanded Disability Status Scale (EDSS), Brief International Cognitive Assessment for Multiple Sclerosis [45] (BICAMS), Backward Corsi [34], 6-Minute Walk Test [46] (6MWT), 25-Foot Walk Test (25FWT), 9-Hole Peg Test (9HPT), Hospital Anxiety and Depression Scale [47] (HADS), Fatigue Scale for Motor and Cognitive functions [48] (FSMC), Visual Analogue Scale [49] (VAS) on the impact of perceived cognitive symptoms on daily life, Cognitive & Leisure Activity Scale [50] (CLAS) and Godin Leisure-Time Exercise Questionnaire [39] (GLTEQ). Furthermore, the 36-Item Short Form Survey [51] (SF-36) and Multiple Sclerosis Impact Scale-29 [52] (MSIS-29) will be completed by Dutch-speaking participants and the Sclérose En Plaques-59 [53] (SEP-59, a combination of the SF-36 and MS-specific questions) will be completed by French-speaking participants. All tests will be carried out at the start of the trial, after 12 weeks of training, at 24 weeks and 64 weeks.

Furthermore, MRI and EEG data will be collected at the start of the trial and after 12 weeks of training, with an additional MRI exam at 24 weeks.

### MRI of the brain

MRI analyses will be carried out at the Universitair Ziekenhuis Brussel on a GE SIGNA Premier 3T MRI scanner using a 48-channel head coil. Scans will be performed at the start of the trial, after 12 weeks of training and at 24 weeks. The following images will be acquired: a high-resolution 3D T1 scan (echo time (TE) 3.0ms; repetition time (TR) 7.3ms; flip angle = 12°; field of view = 256 × 256mm^2^; acquisition matrix = 256 × 256; 180 slices; slice thickness = 1.0mm; bandwidth = 244.1 Hz/pixel; acceleration factor 1.5 × 1.5; scanning time = 4m08s. Images will be reconstructed to a 512 × 512 × 360 matrix), a high-resolution 3D T2 FLAIR scan (TR = 7800ms; TE = 124ms; echo train length (ETL) = 222; field of view = 256 × 230mm^2^; acquisition matrix = 256 × 256; 170 slices; slice thickness = 1.0mm; bandwidth = 390.6 Hz/pixel, acceleration factor 4.6 using HyperSense; scanning time = 4m13s. Images will be reconstructed to a 512 × 512 × 172matrix), a multi-shell high angular resolution diffusion-weighted imaging dataset (HARDI, TR = 4716s; TE = 71.4ms; field of view = 220 × 220mm; acquisition and reconstruction matrix = 128 × 128; 80 slices; slice thickness/gap = 1.7/0.0mm; 16 directions with *b*=700 s/mm^2^, 30 directions with *b*=1200s/mm, 50 directions with *b*=2800s/mm^2^; 5 *b*=0 images interleaved, hyperband factor =3, bandwidth = 3906.25 Hz/pixel; scanning time = 7m52s) along with a phase reversed volume with *b* = 0 and a 3D-QALAS (TR = 5000ms; TE = 1.9ms; inversion time = 100ms; ETL = 150; flip angle = 4; field of view = 256 × 256 × 150mm; cycle time = 900ms; bandwidth = 454.5Hz/pixel; acquisition and reconstruction resolution = 1.0 × 1.0 × 1.0mm; acceleration factor 2.6 using HyperSense; scanning time = 7m38s), to acquire quantitative maps and perform synthetic MRI. The diffusion directions will be calculated using a bipolar electrostatic repulsion model, as implemented in mrtrix [54–56]. Fibre cross-section (FC) and apparent fibre density (FD) will be investigated in white matter through a fixel-based hARDI analysis [57]. The following parameters will be assessed: diffusion tensor image (DTI) parameters (fractional anisotropy (FA) and mean diffusivity (MD)) derived from the *b*=700 s/mm^2^ images, graph theoretical metrics (average path length, edge strength, clustering coefficient, smallworldness and modularity, ratio of inter- versus intrahemispheric connectivity strength), lesion volume, cortical volume and volumes of white matter and deep grey matter. See below for more details.

### EEG

EEG recordings will be made at the start of the trial and after 12 weeks of training. Measurements will be obtained using a portable recording setup with 64 EEG sensors, with horizontal and vertical eye movements and electrocardiography (ECG) leads. Sampling frequency will be 512 Hz. Resting-state EEGs will be recorded, as well as task-related EEGs with the following paradigms: auditory P300 paradigm [58], n-back test [59] and adjusted symbol digit modalities test (SDMT) [60]. Event-related potentials, as well as the following graph theoretical metrics will be assessed: average path length, edge strength, clustering coefficient, smallworldness and modularity and ratio of inter- versus intrahemispheric connectivity strength. See below for more details.

### Sample size

We calculated the minimal sample size with G*Power [61], using an ANOVA design (repeated measures, within-between interaction) with a power of 95% and an alpha error rate of 5%. Under the assumption of a large effect size (*f* = 0.40, based on the change in digit span backwards score after cognitive training [62]) and moderate correlation between the pre- and post-training measurements (*r* = 0.50), the required sample size is 30. Under the less favourable assumption of a medium effect size (*f* = 0.25) and a small correlation among repeated measurements (*r* = 0.30), the required total sample size is 90. In this study, we chose a total sample size of 90, with 30 subjects in each group.

### Blinding and statistical methods

The study will be blinded: patients will not be made aware of the rationale and predictions of the study (pseudo-blinding). The randomisation procedure and the teleconsultations will be carried out and communicated to participants by a trained MS nurse, while the baseline and follow-up testing and analyses are carried out by an investigator who is blinded to the treatment allocation of the patients. Unblinding will only be done in the unlikely case of serious adverse events.

Differences between the different treatment groups in the clinical endpoints compared to baseline will be assessed with a one-sided ANOVA repeated measures test with a within-between interaction. A type I error probability of 0.05 will be used for the main effects and interaction effects. We will correct for multiple comparisons in the post hoc analyses via a family-wise error rate. Per-protocol analyses will be performed, and to correct for missing data, analyses will be repeated using the last observation carried forward method. In case of dropout before the second follow-up testing at 24 weeks, the differences in clinical endpoints at week 12 compared to baseline will still be assessed.

Furthermore, we will identify mechanisms of improvement using graph theoretical analysis. We will pre-process the EEG data in the Oxford Centre for Human Brain Activity (OHBA) software library (OSL 2.0), first using opt (OSL’s pre-processing pipeline), then using oat (OSL’s analysis tool). We will use independent component analysis to denoise recordings. Then, we will identify and regress out artefactual independent components by their degree of correlation with electrooculography (EOG) and ECG and by their degree of kurtosis (eliminating both extreme high and low kurtosis). Then, we will calculate a panel of potential EEG markers of cognitive performance, derived from network EEG analysis. From the pre-processed EEG, we will extract 4-second epochs. This epoch length is an adequate compromise between frequency resolution and minimisation of data loss. These epochs will enter a window-based network construction with the electrodes treated as nodes, calculated using the mutual information edge detection. From the diffusion-weighted imaging dataset, we will derive structural network information via probabilistic tractography and a pre-defined atlas. Graph theoretical metrics calculated for both functional (EEG) and structural (diffusion weigthed imaging) measures allow us to summarise the functional and structural networks in a small number of features. Next to traditional features (average path length, edge strength, clustering coefficient, smallworldness and modularity), ratio of inter- versus intrahemispheric connectivity strength will be assessed.

Finally, we will identify predictors of treatment response by using logistic regression. To account for possible non-linear correlations, we will use machine learning, more specifically random forest classifiers.

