Date of first enrolment	1 September 2022
Target sample size	90
Recruitment status	Recruiting
Primary outcome(s)	Change in digit span backwards post- compared to pre-treatment
Key secondary outcomes	Change in other cognitive scores (BICAMS, backward Corsi), physical scores (EDSS, 6MWT, 25FWT, 9HPT), questionnaires (HADS, FSMC, VAS, SF-36, MSIS-29, SEP-59, GLTEQ, CLAS), MRI and EEG parameters

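### The planned pre-post repeated-measures interaction is a change-score test: valid and correctly sized, but less precise than ANCOVA adjusting for the baseline score the trial already collects

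*Protocol article*

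**What the plan says.** Blinding and statistical methods states: "Differences between the different treatment groups in the clinical endpoints compared to baseline will be assessed with a one-sided ANOVA repeated measures test". The effect tested is the group-by-time interaction. The registration data set gives the primary outcome as "Change in digit span backwards post- compared to pre-treatment". The Sample size section sizes the trial for the same interaction test at 95% power and 5% alpha. Its cautious scenario assumes "a medium effect size (*f* = 0.25) and a small correlation among repeated measurements (*r* = 0.30), the required total sample size is 90"; its favourable one assumes f = 0.40 and a "moderate correlation between the pre- and post-training measurements (*r* = 0.50), the required sample size is 30". The decision follows the cautious scenario: "we chose a total sample size of 90, with 30 subjects in each group".

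No baseline-adjusted model is named. Baseline cognition is one of five factors in the allocation by minimisation (Trial design; Intake and intervention). Digit span backwards is measured at screening, where a z-score between -3 and -0.5 is required for entry. The schedule table marks neuropsychological tests at both the screening point (-T1) and T0.

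**The concern.** With one measurement before and one after training, the group-by-time interaction depends on the data only through each patient's change. A change score subtracts the whole baseline value, as if the slope of post on pre were 1. When pre and post are only weakly correlated, that slope is well below 1, and the subtraction adds baseline noise to the comparison. The plan assumes correlations of 0.30 and 0.50, a range in which the loss can be substantial. At stake is the precision of the primary comparison of combined training with each single training, in a trial with 30 patients per arm.

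**Working it through.** **Inputs.** From Sample size: 3 groups of 30, f = 0.25 with r = 0.30, f = 0.40 with r = 0.50, power 95%, alpha 5%. From Participants: entry band z = -3 to -0.5. An F test with 2 numerator df has no direction, so the one-sided wording is read as the upper 5% tail of F.

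**1. Reproduce the plan's figure.** For the interaction, λ = f²·N·m/(1 - r), df1 = (k - 1)(m - 1), df2 = (N - k)(m - 1).
- With k = 3, m = 2, N = 90: λ = 0.0625 × 90 × 2 / 0.70 = 16.07 on 2 and 87 df. Power is 95.1%, and 90 is the smallest N reaching 95%.
- The favourable scenario gives 28, or 30 with equal groups, as stated.
- Three or four measurements give 72 or 61-63 instead of 90; alpha 0.10 gives 76-78.

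The calculation is therefore the two-time-point interaction, which is the change-score test.

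**2. Error variance with equal pre and post SDs (σ).** Change: 2(1 - r)σ². ANCOVA: (1 - r²)σ². Ratio: (1 + r)/2.

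| r | Change | ANCOVA | Ratio | Reduction |
|---|---|---|---|---|
| 0.30 | 1.40σ² | 0.91σ² | 0.65 | 35% |
| 0.50 | 1.00σ² | 0.75σ² | 0.75 | 25% |

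A simulation of 20,000 trials with 30 per arm, which includes the cost of estimating the slope, gave ratios of 0.655 and 0.762.

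**3. Unequal SDs.** With q = SD(pre)/SD(post), the ratio is (1 - r²)/(q² + 1 - 2rq). At r = 0.30 and assumed q = 0.8: 0.91/1.16 = 0.78, a 22% reduction. At assumed q = 0.6: 0.91/1.00 = 0.91, a 9% reduction.

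**4. Effect of the entry band.** Assume a standard normal score truncated to -3 to -0.5; its variance is 0.249 (SD 0.50).
- *Screening score used as baseline.* At unrestricted r = 0.30 the post variance is 1 - 0.09 × 0.751 = 0.932 and the covariance is 0.30 × 0.249 = 0.075. The change variance is 0.249 + 0.932 - 0.149 = 1.032, against 0.91 for ANCOVA: a 12% reduction. At r = 0.50 it is 0.812 against 0.75: 8%.
- *T0 is a separate retest*, with equal correlations among screening, T0 and post. Pre and post SDs stay equal and r falls from 0.30 to 0.249, so the ratio is 1.249/2 = 0.625: a 37.5% reduction. From 0.50, r falls to 0.384 and the ratio is 0.692: 31%.

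**5. Power at the plan's own effect.** With equal SDs, ANCOVA multiplies λ by 2/(1 + r): 16.07 × 2/1.30 = 24.73 on 2 and 86 df. Omnibus power rises from 95.1% to 99.5%. ANCOVA would reach 95% with about 60 patients.

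**6. Power for one contrast** (30 per arm, two-sided 0.05, unadjusted for multiplicity, r = 0.30, equal SDs). The standard error is √(2 × 1.40/30) = 0.306 SD for change and √(2 × 0.91/30) = 0.246 SD for ANCOVA. The document states none of these differences in SD units. The 1.06 SD is what f = 0.25 implies if one arm differs from two equal arms: 20D²/1.40 = 16.07 gives D = 1.06. The other two are assumed.

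| Difference | Change | ANCOVA |
|---|---|---|
| 1.06 SD | 93% | 99% |
| 0.67 SD (assumed) | 58% | 77% |
| 0.5 SD (assumed) | 37% | 52% |

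**The case against.** The strongest reply is that nothing here is an error. The outcome definition, the sample size and the test agree with one another, the change-score estimate is unbiased under randomisation, and the trial has 95% power at its chosen effect. All of that stands. A reader might infer that 90 patients is wrong or that the trial is underpowered; the reproduced calculation contradicts the first, and the second follows only from effects smaller than f = 0.25, which the document does not state.

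A reader might also take 35%, or its equivalent of 90/0.65 = 138 patients, as a firm figure. It needs equal SDs and the lower of the plan's two correlations. Nor does the narrow entry band simply worsen the change score by lowering r: if the screening score is the baseline, its SD narrows too and the gain shrinks to about 8 to 12%.

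Chance baseline differences are already limited, because allocation balances on baseline cognition. This weakens any argument from imbalance, but it does not give the change-score test the smaller residual variance of ANCOVA.

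Finally, covariates are often left to an analysis plan that is not shown here. That does not dispose of the point, because the article does fix the test and sizes the trial for it.

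**Conclusion.** The point holds as one of efficiency, not of validity, bias or sample size. The primary pre-post test is a change-score test, and baseline-adjusted ANCOVA is asymptotically never less precise in a randomised comparison. On the plan's correlations with equal SDs, the error variance falls by 25 to 35%. Allowing for the entry band under an assumed truncated normal model, the range is about 8 to 12% with the screening score as baseline and about 31 to 37.5% with a separate T0 retest. The schedule table points to a separate T0 assessment, but the article does not say outright that digit span backwards is repeated then.

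The practical gain is small at the plan's own effect (omnibus power 95.1% to 99.5%) and larger if the true effect is smaller (about 58% to 77% for one contrast at an assumed 0.67 SD). The equivalence with change scores applies to the two-time-point primary comparison, not to an omnibus interaction over all four visits. Because the improvement needs no new data, the change is worth making.

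**What to change.** Specify the primary analysis as an ANCOVA of the post-training digit span backwards score (week 13 in the schedule) on arm, with the T0 score as covariate. Report the planned contrasts of combined training against cognitive training and against motor training, with the family-wise correction the plan already announces. State that the baseline is the T0 score and not the screening score. Fix this before any unblinded analysis, so that the choice cannot appear data-driven.

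A mixed model over the follow-up visits with baseline adjustment is a reasonable alternative, but it is not strictly equivalent when visits are missing. The same adjustment can be used for the secondary clinical outcomes; there the gain depends on each outcome's own pre-post correlation and may be smaller (at an assumed r = 0.8 with equal SDs, 1 - 1.8/2 = 10%).

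The cost is a change of wording in the analysis section. It needs no extra patients, visits or measurements, provided digit span backwards is indeed administered at T0.

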**Discussion:**

We hypothesise that the improvement in digit span backwards after 12 weeks of treatment will be significantly higher in the group treated with the combined cognitive-motor telerehabilitation programme, compared to the groups receiving only cognitive and only motor training.

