### Trial design

CoMoTeMS (Cognitive-Motor Telerehabilitation in Multiple Sclerosis) is a two-centre, randomised, controlled, parallel-group and blinded clinical trial, consisting of one intervention group and two active control groups. Recruitment will start in July 2022 in the Universitair Ziekenhuis Brussel (academic hospital) and the National Multiple Sclerosis Center Melsbroek (specialist hospital). In total, 90 patients with clinically definite multiple sclerosis (based on the revised McDonald criteria 2017 [31]) will be randomised to receive either combined cognitive-motor training, cognitive training or motor training, stratified by age, sex, education and baseline activity level and cognition. This study was approved by the ethics committees of the Universitair Ziekenhuis Brussel (B.U.N. 1432022000107) and the National Multiple Sclerosis Center Melsbroek and is registered at ClinicalTrials.gov (NCT05355389, 2 May 2022). The study will be conducted in accordance with the Declaration of Helsinki, the guidelines of the International Conference on Harmonization of Good Clinical Practice (ICH-GCP) and the applicable Belgian legislation. All participants are required to give written informed consent before inclusion.

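### The three-arm interaction test is called one-sided but has no direction, and the stated 95% power does not apply to showing that combined training beats each single training

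*Protocol article*

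**What the plan says.** The Abstract (Discussion) states a directional hypothesis in two parts: improvement in digit span backwards will be greater with combined training "compared to the groups receiving only cognitive and only motor training". The main Discussion repeats this aim. Trial design describes the study as "consisting of one intervention group and two active control groups", and the registration data set gives the primary outcome as "Change in digit span backwards post- compared to pre-treatment".

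Under Blinding and statistical methods, differences between groups "will be assessed with a one-sided ANOVA repeated measures test with a within-between interaction". The section continues: "A type I error probability of 0.05 will be used for the main effects and interaction effects". Pairwise comparisons enter in one sentence: "We will correct for multiple comparisons in the post hoc analyses via a family-wise error rate". It does not say which pairs, which procedure or which sidedness, or whether both comparisons must succeed.

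Sample size uses the same within-between interaction at 95% power and 5% alpha, with no sidedness given. It gives 30 patients for f = 0.40 and r = 0.50, and 90 for f = 0.25 and r = 0.30, and concludes: "we chose a total sample size of 90, with 30 subjects in each group".

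**The concern.** The stated test and the stated hypothesis do not match. The hypothesis needs two directional results, combined over cognitive and combined over motor. The test asks one question without direction: are the three mean changes all equal? Rejecting that does not say which arm is better.

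The gap matters in this trial. The main Discussion chose digit span backwards because gains seem limited to trained functions, and the motor-only arm receives no working-memory training. A significant interaction driven by a poor motor-only arm, with combined and cognitive training alike, is therefore a realistic outcome. It would count as a positive test without supporting the claim.

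The word *one-sided* adds a second problem: an analyst has to guess what to do with it.

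**Working it through.** **Inputs.** Three arms (Trial design); 30 per arm, f = 0.25 with r = 0.30, f = 0.40 with r = 0.50, power 95%, alpha 5% (Sample size); pre-to-post change, so two time points (registration data set). No dropout allowance is stated, so none is applied.

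**Degrees of freedom.** The group-by-time interaction has (3 − 1)(2 − 1) = 2 numerator df.

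**Reproducing the plan's figures.** For the repeated-measures within-between interaction with k groups and m times, the noncentrality is λ = f²·N·m/(1 − r), with df (k − 1)(m − 1) and (N − k)(m − 1).

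- f = 0.25, r = 0.30, N = 90: λ = 0.0625 × 90 × 2 / 0.70 = 16.07; df 2 and 87; power 95.1% (94.4% at N = 87).
- f = 0.40, r = 0.50, N = 30: λ = 0.16 × 30 × 2 / 0.50 = 19.2; df 2 and 27; power 96.8%.

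Both stated sizes are matched exactly by the ordinary F test at alpha 0.05. Other settings do not match:

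| Setting (3 groups) | N at f = 0.25, r = 0.30 | N at f = 0.40, r = 0.50 |
|---|---|---|
| 2 times, alpha 0.05 | 90 | 30 |
| 2 times, alpha 0.10 | 78 | 24 |
| 3 times, alpha 0.05 | 72 | 24 |
| 4 times, alpha 0.05 | 63 | 21 |

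The trial was therefore sized for a non-directional test of the pre/post change.

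**What halving p would do.** p/2 < 0.05 is the same as p < 0.10, so the type I error of the F test would be 10%.

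**What the F test can and cannot show.** On the change score the plan's effect is f = √(λ/N) = √(16.07/90) = 0.423. Different patterns of means give this same f. The patterns are assumptions; d is in SDs of the change score.

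- Combined better than two equal single arms: the SD of the means is D√2/3, so D = 0.423 × 3/√2 = 0.90.
- Arms equally spaced, combined best: the SD of the means is (D/2)√(2/3), so D = 1.04 overall and 0.52 against the nearer arm.
- Combined equal to cognitive, both 0.90 above motor.
- Combined 0.90 below two equal single arms.

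Simulated rejection rates (100,000 replicates, 30 per arm, pooled variance). The last two columns give the chance that both contrasts are significant in favour of combined training:

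| Pattern | Omnibus F at 0.05 | Both, each at two-sided 0.05 | Both, Bonferroni over three pairs |
|---|---|---|---|
| Combined best, single arms equal | 95% | 88% | 75% |
| Equally spaced, combined best | 95% | 50% | 33% |
| Combined ties with cognitive | 95% | 2.5% | 0.8% |
| Combined worst | 95% | 0% | 0% |

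The F test does not distinguish the four rows. The hypothesis is true only in the first two.

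**The case against.** The strongest reply is that the plan is conventional and only loosely worded. Three parts of it deserve weight.

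First, an F test always rejects in its upper tail, and *one-sided* may mean no more than that. The article fixes alpha at 0.05 for the interaction, nowhere mentions halving p, and has a sample size that matches alpha 0.05. A reader might infer that the primary test runs at 10%. The documents do not support this; the 10% is conditional on a procedure they do not describe.

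Second, a reader might infer that the plan cannot show superiority over each single training. That goes too far. Corrected post hoc comparisons are planned, there are only three pairs, and the hypothesis identifies the two that matter. The correction procedure can properly be left to a fuller document. The Bonferroni figures above illustrate one choice. With three arms, an omnibus gate followed by unadjusted pairwise tests also controls the family-wise error, and in the simulation it wins both contrasts about as often as the uncorrected pair (87.7% and 50.3%).

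Third, a reader might take the 0.05 level for main effects to mean that a time effect would count as efficacy. No section says so. Practice effects and regression to the mean are expected equally in randomised arms and do not bias the interaction.

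What remains is in the article's own text: a directional label on a test without direction, a headline test that does not answer the hypothesis, and a power figure for that test only.

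**Conclusion.** The point holds in this form. *One-sided* has no directional meaning for the 2-df interaction and should go. The level is right if it means the upper tail, and 10% if it is applied by halving p. Under either reading, a significant interaction does not show that combined training beats both single trainings, because the F test rejects about 95% of the time at the plan's effect size wherever the combined arm lies.

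The sample-size arithmetic is correct, but its 95% belongs to the omnibus test. For the trial's own claim, power at 30 analysed patients per arm is about 88% or 50% with each contrast at two-sided 0.05, and about 75% or 33% with Bonferroni over three pairs. The first figure in each pair assumes equal single arms, the second equally spaced arms. All rest on f = 0.25 and r = 0.30, normal change scores with common variance, and no dropout.

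**What to change.** Delete *one-sided* from the description of the F test, and replace the primary analysis with text such as:

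> The primary analysis consists of two pre-specified contrasts on the pre-to-post change in digit span backwards at the post-training visit: combined vs cognitive training and combined vs motor training, each tested at two-sided 0.05. The trial is positive only if both favour combined training.

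Because both must succeed, no alpha split is needed between them. Keep the omnibus interaction and the remaining comparisons as secondary, with the family-wise correction.

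Restate the power in Sample size for this criterion at 30 per arm, with the assumed patterns of means: about 88% (single arms equal) and about 50% (equally spaced).

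The change needs no extra visits or measurements, but it is more than rewording, because the power claim falls below 95%. If 95% is wanted for the both-must-succeed criterion, 30 per arm is too few under either pattern. The change should be fixed before outcomes are compared by arm.

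### For the primary week-12 claim the planned family-wise correction is unnecessary and, depending on the procedure chosen, can cost up to 17 points of power

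*Protocol article*

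**What the plan says.** Under Blinding and statistical methods, the protocol article compares the groups on the clinical endpoints with a "one-sided ANOVA repeated measures test with a within-between interaction". It continues: "A type I error probability of 0.05 will be used for the main effects and interaction effects". The next sentence is: "We will correct for multiple comparisons in the post hoc analyses via a family-wise error rate". The correction method, the family and the number of comparisons are not named, and the post hoc tests are not made conditional on a significant F test.

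The hypothesis, in the Discussion part of the abstract, is that improvement at 12 weeks will be "significantly higher in the group treated with the combined cognitive-motor telerehabilitation programme, compared to the groups receiving only cognitive and only motor training". The registration data table defines the primary outcome as the post- versus pre-treatment change in digit span backwards. The Primary outcome parameter section has the test repeated at 24 and 64 weeks. The Sample size section sets 90 patients, 30 per arm.

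**The concern.** The comparisons of combined training with cognitive-only and with motor-only training carry the trial's conclusion. The correction sentence covers them along with every other post hoc test. For a claim that needs both to succeed, a correction protects against an error that is already bounded. It still raises the threshold each test must pass. If the procedure later chosen is a common single-step one, the trial could miss a benefit that the same 90 patients would show under an equally valid rule.

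**Working it through.** **Inputs.** From Sample size: f = 0.25, r = 0.30, N = 90, 30 per arm, power 95%, alpha 5%. From the registration data table: one pre-post change, so m = 2 measurements. Assumed here: two-sided 0.05 for the pairwise tests (their sidedness is not stated), analysis of change scores with 87 error df, and two patterns of arm means, because the protocol gives none.

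**Step 1: reproduce the plan's sample size.** For the within-between interaction, lambda = N·m·f²/(1 − r), with 2 and N − 3 df.
- f = 0.25, r = 0.30, N = 90: lambda = 90 × 2 × 0.0625/0.70 = 16.07, power 0.951. At N = 87 power is 0.944, so 90 is the smallest equal-arm total.
- f = 0.40, r = 0.50: N = 30 gives 0.968 and N = 27 gives 0.947, so 30 is reproduced.
- Three or four measurements would give 72 or 63, not 90. The plan was sized for a single change score.

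**Step 2: does the primary claim need a correction?**
- *Both must succeed.* A false claim requires at least one of the two nulls to be true and that true null to be rejected. Its probability cannot exceed the level of that one test, with or without an F gate. In simulation, with combined equal to cognitive-only and motor-only far lower, combined is falsely declared better than both in 2.5% of trials unadjusted and in 0.8% with Bonferroni.
- *F gate.* With three arms and one change score, if any two pairwise nulls hold then all three arms are equal, which is what F tests. F at 5% followed by unadjusted pairs gives a simulated family-wise error of 5.0% when all arms are equal and 5.0% when one pair is equal.

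**Step 3: what a correction would cost.** In SD units of change, lambda = 30·Σ(arm mean − grand mean)².
- Combined above two equal arms: 20d² = 16.07, so d = 0.896.
- Equally spaced arms: 15D² = 16.07, so D = 1.035 between extremes and 0.518 between neighbours.

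Simulated power to beat both comparators, F test at 5% first:

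| Rule for the pairs | Two equal comparators | Equally spaced |
|---|---|---|
| Unadjusted | 87.6% | 50.5% |
| Bonferroni, 3 pairs | 75.3% | 33.3% |
| Tukey | 77.2% | 35.4% |
| Holm, 3 pairs | 80.5% | 43.1% |
| Shaffer | 86.5% | 50.2% |
| Holm, 2 key contrasts | 87.4% | 50.5% |

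Without the F gate, the unadjusted figures are 87.9% and 50.6%.

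Hand check of the spaced case: the standard error of a difference is √(2/30) = 0.258, so the neighbouring contrast sits at 0.518/0.258 = 2.00 standard errors. The critical value is 1.988 unadjusted (power about one half) and 2.441 with Bonferroni (about one third).

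**Step 4: where the correction is needed.**
- Three unadjusted pairs without a gate have a family-wise error of about 12%.
- With three arms and four visits, a significant interaction F (6 df) followed by unadjusted pairs at each follow-up gives a family-wise error of 24% if the effect exists at week 12 only, and 19% if it exists at weeks 12 and 24.

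**The case against.** The strongest objection is that the sentence names no procedure. Holm, Shaffer or a closed test would each satisfy it, and the choice may properly be left to the statistical analysis plan. This stands. A reader might infer from the Bonferroni and Tukey figures that the key tests will run far below 5%. When combined equals cognitive-only and motor-only is far lower, the two-sided error of that comparison is indeed 1.7% under Bonferroni and 1.9% under Tukey, but it is 5.0% under Holm and Shaffer. The protocol commits to none of these.

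A reader might also infer that the F test already controls the error, so the correction can go altogether. The document does not support that. It does not make F a gate, it applies the ANOVA to several clinical endpoints, and it schedules three follow-up visits; step 4 shows the error this would allow. If F spanned all four visits, an effect at a later visit could open the gate while the arms are equal at week 12. Two unadjusted week-12 tests sharing an arm would then have about 9.0% family-wise error, although the claim needing both would stay protected.

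The size also depends on the scenario. Under the plan's favourable inputs (f = 0.40, r = 0.50) with 90 patients, power to beat both is about 100% under either rule with equal comparators, and 96% against 91% (Bonferroni) with equal spacing.

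What survives is that the sentence as written takes in the two primary contrasts, for which no correction is needed.

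**Conclusion.** The point holds for the baseline-to-week-12 primary contrasts only. There the correction is unnecessary, and the cost of keeping it depends on a procedure that the protocol leaves open. At f = 0.25, r = 0.30 and 30 per arm:
- Bonferroni, Tukey or Holm over three pairs loses 7 to 12 points if the comparators are equal, and 7 to 17 points if the arms are equally spaced.
- Shaffer, or Holm over the two key contrasts, loses about 0-1 point.

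The equally spaced pattern is an assumption. So are two-sided pairwise tests and the reading of the hypothesis as requiring superiority over both comparators. If the sponsor wants to claim superiority over either comparator alone, the both-must-succeed argument no longer applies, and some family-wise control is needed.

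The written rule is conservative and does not inflate the type I error. This is an avoidable loss of power, not an invalid analysis.

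**What to change.** For the primary endpoint only, state in Blinding and statistical methods, or in the statistical analysis plan: combined versus cognitive-only and combined versus motor-only are each tested on the baseline-to-week-12 change in digit span backwards at two-sided 0.05 without further adjustment; superiority is concluded only if both are significant.

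If an F test is kept as a gate, specify that it is the three-arm test on the baseline-to-week-12 change only. Keep the family-wise correction, with its procedure named, for the 24- and 64-week visits, the secondary endpoints and any other pairwise claim.

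The cost is a few sentences of text before unblinding. No patients, visits or procedures are added, and the error of the primary claim stays at or below 5%.
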